### Phase I data analysis

Focusing on the 32 study schools, multilevel models will be developed to estimate the linear increase in student outcomes per 10% point increase in FSM uptake at school levels, accounting for clustering (schools) and adjusted for both the routinely observed school-level and student-level characteristics (including FSM eligibility). Given these adjustments, the increase in student outcomes per 10% point increase in FSM uptake will reflect FSM uptake that is potentially modifiable by school-level policy. A further exploratory analysis will consider FSM uptake and association with aggregated (at school level) attendance and educational outcomes.

In addition to the main analyses, which will include all students, regardless of FSM eligibility, multilevel linear regression models will be used to calculate the mean difference in outcomes (including diet and food insecurity) comparing students taking FSM and those not taking FSM within FSM-eligible participants only, adjusting for school-level and student-level characteristics and clustering.

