Furthermore, there is a paucity of evidence on the economic impact of the current UK FSM policy, with no studies evaluating policy cost-effectiveness.^31^ Food insecurity is being exacerbated by the current cost of living crisis,^32 33^ making it imperative that one of the main government policies to tackle food insecurity, means-tested FSM, is fit for purpose. There has been a call to expand FSM to more or all children at school,^34^ due to the food insecurity experienced in children of households with low income who fall outside of the current eligibility criteria, and it is important to understand the potential impact of this and to have robust data on which policy change could be modelled.

The aim of the CANTEEN study is to evaluate the effectiveness and cost-effectiveness of the current means-tested FSM policy in UK secondary schools on diet and food insecurity outcomes, understand what factors are associated with uptake, and model the potential impact of the proposed policy change.

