### Phase I data collection

#### Student outcomes

Dietary intake will be collected at each of two student data collection visits, using an online self-completion 24-hour dietary recall tool called Intake24.^45^ This is a validated dietary assessment tool, having been assessed to give close estimates of both macro and micronutrient intakes, within the specific age groups being included in this study.^46^,^48^ Intake24 is the dietary assessment platform used by the UK National Diet and Nutrition Survey.^12^ Students will complete each 24-hour recall during timetabled sessions with researchers present on non-consecutive school days. From the Intake24 data, FV intake will be calculated (according to National Diet and Nutrition Survey methods^49^) over a 24-hour period at school as well as outside of school. Other dietary measures that will be explored as secondary outcomes will include calculation of diet quality^50^, meeting the 5-a-day FV recommendation, intake of energy, dietary fibre, free sugars and other key micronutrients and macronutrients. FV will be measured as portions (for FV) and nutrients as µg/mg/g and also expressed as a percentage of energy intake. Consumption will be explored at school and over 24 hours. Dietary intake variables will be averaged over the 2 days of data collection to account for daily variation.

Food insecurity will be a further secondary outcome and will be measured at the first data collection visit using the 9-item Child Food Security Survey Module, which has been validated in adolescents.^51 52^ At this visit, data will also be collected on demographics (age, name, DOB (for linkage to parent outcomes only), gender, ethnicity) and postcode (Index of Multiple Deprivation), usual school lunch consumption (ie, school food or food brought in from home or purchased outside of school), FSM eligibility and uptake, money spent on food outside of school, quality of life (Child Health Utility 9D (CHU-9D))^53^ and physical activity (Single-item minutes based assessment^54^). Students will be asked at this stage whether they are willing to be contacted for future focus group participation if their school is later selected as a case study school. The total data collection time for the first visit will be approximately 60–90 min, and for the second visit, approximately 30 min.

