### Strengths and limitations of this study

This research will provide critical evidence on the impact of a key UK policy that is designed to mitigate inequalities by evaluating the current, means-tested FSM policy on diet quality and food insecurity outcomes in secondary school students in the UK. The study design includes both quantitative and qualitative research to provide a thorough and in-depth analysis understanding of the effectiveness of FSM policy. Economic evaluation will determine the cost-effectiveness of the current means-tested FSM policy. The study design includes both quantitative and qualitative research and will gather data from a wide range of stakeholders to explore the factors associated with FSM uptake and to provide a thorough and in-depth analysis and understanding of the effectiveness of FSM policy.

However, there are a number of limitations to consider. The current nature of the policy precludes the use of randomised controlled trial methodology, and therefore, the design is observational and cross-sectional in nature, which limits inferences about the causality in the relationship between FSM participation, diet quality and food security. The study is based on self-report questionnaires for students, parents and staff members and, particularly for the dietary data from students, is susceptible to reporting and recall bias leading to a decrease in data validity. Fieldwork will only be conducted in two geographical areas of the UK (Midlands and NI), although these are diverse, and so findings may not be generalisable to the wider context of the UK as there may be socioeconomic/cultural differences which affect the uptake of FSM. Canteen observations, although collected using standardised templates and methodology, could potentially be biased by researchers’ interpretations. The limited coverage of the case study schools (n=6–8) may not provide the full spread of contextual factors that influence FSM uptake. Finally, the economic assessment, although informative, may not capture nuanced social and cultural factors driving the consumption of diet and food insecurity.

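### The eligible-only comparison of FSM takers with non-takers does not separate within-school from between-school differences, so a school-level uptake gradient can leak into the student-level result

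*Protocol article*

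**What the plan says.** Under Phase I data analysis, the main multilevel models "estimate the linear increase in student outcomes per 10% point increase in FSM uptake at school levels". They account for clustering by school and adjust for school- and student-level characteristics. School uptake is therefore the exposure in these models, distinct from the characteristics adjusted for.

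A second analysis is introduced with "In addition to the main analyses, which will include all students, regardless of FSM eligibility". Its method is a linear multilevel model that yields mean differences, and its outcomes cover both diet and food insecurity. The contrast and its adjustment are set out as "comparing students taking FSM and those not taking FSM within FSM-eligible participants only, adjusting for school-level and student-level characteristics and clustering". The article does not give the random-effects structure, list the school-level covariates, or say whether school uptake is among them.

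On timing, Student outcomes states: "Food insecurity will be a further secondary outcome and will be measured at the first data collection visit". The same visit collects "FSM eligibility and uptake, money spent on food outside of school, quality of life" and other items. The limitations section says that the design is cross-sectional, "which limits inferences about the causality in the relationship between FSM participation, diet quality and food security".

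**The concern.** A multilevel model with one coefficient for individual FSM taking combines two comparisons: takers against non-takers in the same school, and students in high-uptake schools against students in low-uptake schools. The second carries whatever differs between those schools and also relates to diet, except what the covariates remove. The study's main hypothesis is that outcomes vary with school uptake, so a gradient of this kind is what its designers expect.

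This is the only analysis in the section that compares eligible students who take the meal with eligible students who do not. Readers will take its coefficient as the student-level result. If part of it is a school-level gradient, the student-level and school-level findings are not separate pieces of evidence, and the student-level figure is shifted towards the school-level one.

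A smaller matter concerns food insecurity. Taking FSM and food insecurity are recorded at the same visit, and an eligible student who is short of food has more reason to take the meal. That difference is harder to read than the diet differences, yet the article gives both the same model and the same wording.

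**Working it through.** **Inputs from the article.** ICC 0.03 and 45 students per school in 32 schools (Sample size calculation). School uptake mean 77%, SD 12% in Northern Ireland, and mean 86%, SD 20% in the Midlands (Study setting). Schools must have more than 20% of pupils eligible (Study setting).

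**Assumptions.** 20% to 40% of sampled students are eligible, giving m = 9 to 18 per school and 288 to 576 in all. The model is a random-intercept model with no school uptake term. The ICC was set for fruit and vegetable intake and is applied to that outcome only.

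**The plan's own figure.** The article states no figure for the eligible-only contrast. Its sample size calculation does reproduce: 304 per group unclustered × design effect (1 + 44 × 0.03 = 2.32) = 705, or 15.7 schools, rounded up to 16 schools and 720 students per group. It does not bear on this point, but it confirms how the ICC and cluster size are used.

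**Formula.** Let μ and s be the mean and SD of school uptake.
- λ = 1 / (1 + m × ICC / (1 − ICC)), the weight that the model leaves on between-school variation
- E = μ(1 − μ) − s², the average within-school variance of taking
- W = E(1 − 1/m), the within-school part
- B = s² + E/m, the between-school part, where E/m is chance variation in small samples
- Leaked fraction = λs² / (W + λB)

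Only s² belongs in the numerator. The E/m part carries weight but no school-level confounding.

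**Northern Ireland figures.** E = 0.1771 − 0.0144 = 0.1627.
- m = 9: λ = 0.782, W = 0.1446, B = 0.0325. Leaked fraction = 0.0113 / 0.1700 = 6.6%.
- m = 18: λ = 0.642, W = 0.1537, B = 0.0234. Leaked fraction = 0.0093 / 0.1687 = 5.5%.

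**Midlands figures.** E = 0.1204 − 0.04 = 0.0804.
- m = 9: W = 0.0715, B = 0.0489. Leaked fraction = 0.0313 / 0.1097 = 28.5%.
- m = 18: W = 0.0759, B = 0.0445. Leaked fraction = 0.0257 / 0.1045 = 24.6%.

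**Total between-school weight**, λB / (W + λB), is 9% to 15% and 27% to 35% respectively. Most of the weight is within-school in every case.

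**Simulation.** 4,000 replicates of a generalised least squares fit with known variance components; 32 schools, 14 eligible students each, uptake mean 80% and SD 16%, SD of the outcome 1.9, and no true individual effect. The assumed school gradient is 1.6 portions/day between 0% and 100% uptake, which is 1.6 × 0.32 = 0.51 portions across two SDs.

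| Model | Mean coefficient | Empirical SE |
|---|---|---|
| Taking only | 0.185 | 0.236 |
| Taking plus school uptake | −0.002 | 0.244 |

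The leaked fraction here is 0.185 / 1.6 = 0.116; the formula gives 0.120. With no gradient, adding school uptake raises the SE from 0.227 to 0.240, about 6%. With the gradient the rise is about 3%.

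**The case against.** The strongest reply is that the article never says the model is a random-intercept model with taking as its only exposure term. It says multilevel linear regression and promises adjustment for school-level characteristics. School uptake is requested from schools, stratifies school selection and is the main exposure, so it could be among those characteristics. If it is, the leak disappears, as the simulation shows. A full protocol or SAP, not shown here, may settle it. This stands in part: a reader may infer that the plan fixes a model that mixes the two comparisons, and the text does not support that. But the section treats uptake as the exposure and the characteristics as something else, so on a plain reading school uptake is not in this model.

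Three other inferences go too far.
- *The school factors behind the gradient are unmeasured.* The article plans direct observation of eating areas, catering and business manager questionnaires, and collection of school food policies and meal data. What is unstated is whether these enter the model.
- *The model amounts to a pooled regression.* It does not: 65% to 91% of the weight is within-school. A leak is also not the same as a material bias; even the assumed gradient of 1.6 gives a bias below one standard error (0.185 against 0.236).
- *The food-insecurity result will show that FSM does harm.* Nothing in the article establishes the direction or size of reverse causation. The contrast is supplementary, school-level uptake is already the main exposure for food insecurity (Abstract, Methods and analysis), and the limitations section already cautions on causality between FSM participation and food security. What is left is how this one difference is labelled.

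**Conclusion.** The concern holds as a cheap improvement to a supplementary analysis. As described, the taker coefficient is not tied to the within-school comparison. Unless school uptake is a covariate, it picks up about 5.5% to 6.6% (Northern Ireland figures) or 25% to 29% (Midlands figures) of any uptake-related school gradient in the outcome.

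These figures rest on the assumed 20% to 40% eligibility, a random-intercept structure that the article does not state, and uptake distributions taken from planning data rather than from the recruited schools. The two sites bracket the answer; a pooled uptake of 80% with SD 16% gives about 12%. The resulting bias depends on a gradient whose size is unknown, so 0.185 portions/day is an illustration and not a forecast.

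The food-insecurity matter is a reporting point only, since the stated aim is to "evaluate the effectiveness and cost-effectiveness of the current means-tested FSM policy in UK secondary schools on diet and food insecurity outcomes" and the general causal caveat is already present.

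**What to change.** In the eligible-only model, add the school's FSM uptake among eligible students, or the school mean of taking among sampled eligible students, alongside the student's own status; school fixed effects would also serve. State that the within-school coefficient is the student-level result. The school mean or fixed effects isolate the within-school comparison directly, while reported school uptake removes a gradient that is linear in uptake.

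No new data are needed, because uptake is already requested from schools. The cost is one covariate and, in the simulation, a 3% to 6% larger standard error. Schools near 100% uptake will contribute little to the within-school estimate, and the report should say so.

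For food insecurity, describe the taker versus non-taker difference as descriptive, note that both are measured at the same visit and that need may drive taking, and point readers to the school-level analysis already planned. This costs a sentence.

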### Economic evaluation

We will undertake a cost–utility analysis of increasing FSM participation. This will be exploratory due to the expected variation in costs and models of FSM implementation, and ranges in assumptions about the persistence of changes in diet and impacts on future health. The resulting estimates will be used to evaluate the cost-effectiveness of FSM participation at increasing quality-adjusted life-years (QALYs). Costs will be calculated as the marginal costs of increasing FSM participation, minus future National Health Service (NHS costs that are foregone as a result of forecast changes in future health. These will be expressed in 2024 pounds sterling. Utility gains will be calculated as the sum of contemporaneous changes in QALYs derived from student completion of the CHU-9D during primary data collection, plus future gains in QALYs estimated based on forecast changes in future health.

### Phase II data collection

Interviews will be undertaken with school stakeholders (eg, catering and business managers; governors; teachers, senior leaders and other relevant school staff; n=4/school) and parents (n=4–8/school), using semistructured topic guides. The aim of these will be to explore views of the FSM system, school and home food environment, and broader school contextual factors (eg, capacity constraints and additional investment requirement to enable higher levels of take-up). Interviews will be offered either via telephone, online or in person, as per the preference of parents and school staff. Each interview will take around 1 hour. Parents will be asked to complete a short survey including questions on ethnicity, gender, age group, child FSM eligibility and family food insecurity after they have signed the consent form if they have not already participated in phase I of the study.

Focus groups will be conducted with students (n=2–4 focus groups/school; n=6–8 students/group invited to ensure participation of n=4–5), ensuring representation of participants both eligible and ineligible for FSM. Scheduling of focus groups will try to ensure discussion among pupils with similar characteristics, for example, age and FSM status. In the focus groups, we will employ creative methods, using characters from the Disney Pixar film, Inside Out 2, sourced from the Be Happy resources,^60^ with the aim of exploring in depth the emotions associated with school food and the school eating environment. Questions will be incorporated within the exercise using hypothetical scenarios to allow consideration of a range of student perspectives, for example, students who take and do not take school meals and who are eligible or not eligible for FSM. Students will be recruited from the classes in which data collection occurred for the quantitative study, with expansion as required should recruitment targets not be met. Focus groups will take place in the school on an agreed date and time. Each focus group will take approximately 1.5 hours.

The school will be asked to provide FSM eligibility and SEN status, gender, age and ethnicity for students who complete the case study and who have not already participated in phase I. Prior to the focus group discussions, all students will be asked for their assent. After providing assent, they will also be asked to state their year group and answer a question about their usual lunchtime eating routine (eg, packed lunch/school lunch/mixed). Interviews and focus groups will be audio-recorded.

### Phase II data analysis

Interviews will be transcribed, anonymised and checked for accuracy by the research team; focus groups will be similar except they will be transcribed by an external transcription service. Thematic analysis techniques will be employed,^61^ which seek to identify and classify the content of qualitative data, to explore patterns and differences across interviews and focus groups, with the aim of providing explanatory conclusions clustered around themes. The transcripts will be coded, then collated into themes and subthemes according to the conceptual similarity of codes. Agreement on concepts and coding will be sought between members of the research team (including across recruitment sites) throughout the analysis process to ensure reliability. A proportion of the data (20%) will be coded by two different team members to check for inter-coder reliability. Thematic analysis will be supported by qualitative analysis software (NVivo).

The sequential nature of the quantitative and qualitative data collection will potentially allow a mixed-methods approach drawing on sequential explanatory design.^62^,^64^ In this way, the qualitative data collection can help explain, or elaborate on, the quantitative results obtained. The quantitative data and their subsequent analysis will provide a general understanding, with the qualitative data and their analysis refining and explaining the results by exploring participants’ views in more depth.^62^,^64^ School factors across the different levels of uptake will be explored, as well as commonalities and differences in factors related to FSM provision and support, allowing characterisation of schools according to these different levels of uptake.

### Data collection tool piloting

The student, school staff, governor, student and parent questionnaires were all piloted with members of the PPIE panel in the relevant groups. Similarly, case study interviews and focus group schedules have all been piloted through the same process. The tools were refined based on the feedback provided.

This research will provide critical evidence on the impact of a key UK policy that is designed to mitigate inequalities by evaluating the current, means-tested FSM policy on diet quality and food insecurity outcomes in secondary school students in the UK. The study design includes both quantitative and qualitative research to provide a thorough and in-depth analysis understanding of the effectiveness of FSM policy. Economic evaluation will determine the cost-effectiveness of the current means-tested FSM policy. The study design includes both quantitative and qualitative research and will gather data from a wide range of stakeholders to explore the factors associated with FSM uptake and to provide a thorough and in-depth analysis and understanding of the effectiveness of FSM policy.

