## Methods and analysis

This is an observational, cross-sectional, multiple-methods study design, with outcomes collected at school, student and parent levels and accompanying economic evaluation. As the FSM policy already exists in the secondary school setting, traditional approaches (eg, a cluster randomised controlled trial) are not possible. The variable levels of FSM uptake will, therefore, be used to explore, both at school and student levels, the association between FSM uptake and dietary and food insecurity outcomes, with analyses adjusted for potential confounders. The primary outcome will be fruit and vegetable (FV) intake (portions/day) as an indicator of diet quality. Data will then be used to model the impact of future policy change.

Phase I comprises recruitment of schools and students in order to collect a variety of quantitative data, including survey and dietary intake data from students, direct observations of the school eating environments, and questionnaires to key staff members and parents. The large variation in FSM uptake seen across schools also offers the opportunity for deeper exploration of barriers and facilitators to FSM uptake and school food systems more generally. Phase II will, therefore, comprise a case study with a small number of schools that will be selected from the schools recruited in phase I. A series of focus groups with students, and interviews with both staff/school stakeholders and parents will be conducted.

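### The article promises to determine the cost-effectiveness of the existing FSM policy, but the planned economic analysis is an exploratory one of raising participation and describes no no-policy comparator

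*Protocol article*

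**What the plan says.** The claim "Economic evaluation will determine the cost-effectiveness of the current means-tested FSM policy" appears in the same words in three places: the strengths and limitations box after the abstract, the closing paragraph of Data collection tool piloting, and the later section Strengths and limitations of this study.

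The aim, at the end of the Introduction and also in the abstract, is to "evaluate the effectiveness and cost-effectiveness of the current means-tested FSM policy in UK secondary schools on diet and food insecurity outcomes". Its verb is *evaluate*, not *determine*, but its object is again the existing policy.

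The section Economic evaluation describes a different analysis: "We will undertake a cost–utility analysis of increasing FSM participation". On its status: "This will be exploratory due to the expected variation in costs and models of FSM implementation". On the cost side: "Costs will be calculated as the marginal costs of increasing FSM participation", with future NHS costs avoided taken off. On the effect side, QALYs come from the CHU-9D now plus forecast later health. The stated use of the result is to judge FSM participation as a way of gaining QALYs.

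On the design, Methods and analysis says: "As the FSM policy already exists in the secondary school setting, traditional approaches (eg, a cluster randomised controlled trial) are not possible". Phase I data analysis then gives two contrasts: the slope of student outcomes on school-level uptake, and takers versus non-takers among eligible students.

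**The concern.** The stated claim and the stated method differ in two ways. The first is certainty: a promise to determine sits beside an analysis that its own section calls exploratory. The second, and more important, is the quantity itself. Whether an existing policy is cost-effective is a question about having it against not having it. Whether raising participation is cost-effective is a question about the next takers, given that the policy exists. These serve different decisions: keep or withdraw in the first case, promote uptake in the second.

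The Introduction says that no study has evaluated the cost-effectiveness of the UK policy, and Ethics and dissemination plans briefings for government. If the wording stands, a cost per QALY for extra participation could be read as the first verdict on the policy as a whole.

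**Working it through.** No figure in the plan is at issue, so the check compares the two quantities.

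**1. What the Economic evaluation section defines.** For an increase in participation:

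marginal ratio = (added cost of higher participation − NHS costs avoided by it) ÷ (QALYs gained from it).

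**2. What the claim requires.** For the policy itself:

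policy ratio = (net cost with the policy − net cost without it) ÷ (QALYs with the policy − QALYs without it).

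**3. Is there a term for the state without the policy?**
- Economic evaluation: none is described.
- Methods and analysis: the policy is already in place in secondary schools.
- Phase I data analysis, first contrast: an uptake gradient between schools that operate the policy.
- Phase I data analysis, second contrast: takers against non-takers among eligible students. Non-takers remain entitled, so this is a participation contrast within the policy. The article does not tie it to the economic analysis.
- Policy modelling (abstract, Introduction, Methods and analysis): concerns proposed or future change, not absence of the current policy.

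**4. When would the marginal ratio equal the policy ratio?** Take the simplest case. Let n students take the meal, F be fixed programme cost, c the cost per taker, s the NHS saving per taker and e the QALY gain per taker, with c, s and e the same for everyone and no effect on non-takers.

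- Marginal ratio = (c − s) ÷ e.
- Policy ratio = (F + n·c − n·s) ÷ (n·e) = (c − s) ÷ e + F ÷ (n·e).

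Even here they differ by F ÷ (n·e), which vanishes only if F = 0. If c, s or e differs between current and additional takers, a further difference arises. With e positive, a positive F makes the marginal ratio lower than the policy ratio. Smaller gains or higher costs among additional takers push the other way.

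**5. Does the article assume these conditions?** No. It points away from at least one: Economic evaluation expects costs and models of implementation to vary, and Phase II data collection will ask about capacity limits and the investment needed for higher take-up. Neither fits comfortably with a constant cost per taker.

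**Result.** The marginal quantity is defined. The policy quantity is not, and it cannot be obtained from the marginal one without added assumptions.

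**The case against.** The strongest reply is that a reader of the methods is not misled. Economic evaluation says openly what will be done and why it is exploratory, and Strengths and limitations concedes limits on causal inference and on what the economic assessment captures. School cost data are to be collected comprehensively, and a full protocol or health economics plan, not shown here, may contain average-cost or reference scenarios. The component is exploratory, and the remedy is wording.

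Part of this stands. Absence of modelling detail from an article would be no finding. But the point does not rest on missing detail: the marginal definition that is stated conflicts with the claim that is stated. The limitations do not mention the mismatch, and the same section repeats the claim.

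Three stronger readings are tempting and are not supported.

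- A reader might infer that benefit to those taking FSM is not estimated at all. Phase I data analysis does plan an adjusted comparison of takers with non-takers among eligible students. It is open to confounding and is not a no-policy contrast, but it is an estimate of that benefit.
- A reader might try to size the problem by running the uptake slope down to zero and quoting the resulting uncertainty in fruit and vegetable portions. That says nothing about cost per QALY. Nor is near-zero uptake wholly outside the planning data: Study setting gives a Midlands range of 3% to 100%, although the NI minimum is 42% and the range in the recruited schools is not given.
- A reader might infer that the aim itself promises a determination. It says *evaluate*, which is compatible with exploratory work; only its object needs changing.

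**Conclusion.** The point holds as a conflict between claim and method. Three statements promise to determine, and the aim sets out to evaluate, a whole-policy quantity; the described analysis explores a marginal one. No numerical size can be given, because the article reports no fixed cost, cost per taker or QALY gain. In the simple case worked above the gap is F ÷ (n·e), and with differing takers its direction is not determined.

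The conclusion assumes that the Economic evaluation section describes the analysis to be run. If the full plan defines a no-policy counterfactual, the article should say so and state its assumptions.

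This is a moderate correction of wording and of what may be concluded. It is not a fault in the primary outcome, sample size, main models or data collection, and it does not make the planned cost–utility analysis invalid for its own question.

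**What to change.** - In the box after the abstract, in Data collection tool piloting and in Strengths and limitations, replace the sentence with a statement that the economic evaluation will explore the incremental cost per QALY of increasing FSM participation under the current policy.
- In the abstract and at the end of the Introduction, change the economic object of the aim in the same way. The verb can stay.
- Add to the limitations that cost-effectiveness of the policy against no policy is not estimated.
- If a whole-policy figure is reported, label it a scenario and list its assumptions on fixed costs, on cost and effect per taker, and on the state without the policy. The alternative is to define that counterfactual in Economic evaluation.

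The cost is a less ambitious stated claim. No data collection or main model changes.
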